### Statistical Analysis

#### Calculation Hypotheses for the Number of Participants Required and the Result

Assuming a correlation coefficient of 0.1 for the within-patient response, 30% ASAS20 responders in the dummy stimulation period vs. 50% with active simulation, and the use of a random intercept logistic model for the statistical analysis using a 5% two-tailed threshold of significance, simulations have shown that a sample size of 90 subjects will provide 80% power for demonstrating the efficacy of active stimulation vs. placebo. Accounting for 25% potential missing values for the primary endpoint (loss to follow up, redrawn consent), we will include 120 patients in the study.

#### Sample Description

The characteristics of patients of each group will be described using descriptive statistics such as percentages for categorical data, means, medians, ranges and interquartile ranges for continuous variables. Groups of patients will also be described at the beginning of each period and of each treatment.

#### Statistical Analysis for the Primary Objective

The main statistical analysis will be performed on all randomized patients according to the Intention-To-Treat principle. A secondary analysis of the main criterion will be performed in the per protocol population comprised of patients having complied with at least 10 weeks of treatment during each treatment period, for whom all the other stipulations of the protocol have been respected and for whom all required data are available.

A subject-specific random intercept logistic model will be used to assess and test, using a 5% two-tailed threshold of significance, the effect of treatment on the percentage of ASAS20 response at the end of each period.

#### Statistical Analysis for the Secondary Objectives

Statistical analysis of secondary binary outcomes (i.e., response according to ASAS40 criteria and partial remission according to the ASAS definition) will be performed using similar random effect logistic models as for the primary objective. Statistical comparison between treatment periods of continuous variables (ASDAS_CRP, ASDAS_ESR, BASFI, BASMI, fatigue (BASDAI 1st question), global pain score, NSAID intake score scores, SF-36, ASQOL, ASAS HI and WPI scores, HAD, CRP serum level, ESR, levels of circulating IL-6, IL-23, IL-17, IL-33, and MMPs) will be performed using random effect linear models.

The analyses for the primary and secondary outcomes will be also performed in subgroups of patients (patients with radiographic forms of the disease and patients with non-radiographic forms of the disease), as sensitivity analyses.

All calculations will be performed using R software version 3.5.1 or later, using lme4 and lmerTest packages for the mixed effects models. Statistical tests will be performed using a Kenward-Roger method for degrees of freedom method estimation.

All statistical comparisons will be performed at the 5% level of significance.

No interim analysis is forecasted.

In case of missing data for the primary assessment criterion, no strategy of imputation is forecasted. We will take into account information available at time of last follow-up.

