## Eligibility Criteria

### Inclusion Criteria

1.Adult patient (18–90 years old) meeting the ASAS classification criteria fo axial SpA, followed for at least 1 year, with radiographic evidence of advanced sacro-illitis, according to modified New-York criteria (van der Linden et al., 1984) (ankylosing spondylitis) or not.2.Patient suffering of active SpA, with or without treatment, having a total BASDAI score ≥4 (0–10) at baseline and a score of global pain ≥4 (0–10).3.Patient insufficiently relieved despite optimal drug management for at least 6 months, including at least 2 different NSAIDs at the maximum tolerated dose for at least 3 months (or less in case of intolerance) and at least two lines of biotherapies, or discontinued SpA treatments due to intolerance, contraindication.

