### Secondary Endpoints

The secondary evaluation criteria for the study (collected at the end of each period) are:

1.Response according to ASAS40 definition, computed in a manner similar to that used to compute the ASAS20 response, except that it required improvement of 40% in (3 of the 4 ASAS domains, with a positive change of (2 units (on a scale of 0–10) in each domain. Absence of deterioration in the remaining domain is required and defined as for the ASAS20 response.2.Partial remission according to the ASAS definition defined as a value of < 2 units (on a scale of 0–10) in each of the 4 ASAS domains (patient’s global assessment, pain, BASFI, and inflammation).3.Change in BASFI.4.Serum CRP level and ESR.5.Change in ASDAS_CRP, ASDAS_ESR.6.The level of IL-6, IL-17, IL-23, IL-33, and MMP-3-8-9.7.SF-36, ASQOL‘.8.ASAS-HI, WPI.9.Fatigue (VAS), Global Pain (VAS).10.HAD.11.BASMI.12.Change in NSAID intake score.

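### Partial remission, and ASAS40 if uncommon, would be tested with an lme4 logistic mixed model whose default Laplace fit becomes unreliable when few patients respond; the fitting method should be fixed as adaptive quadrature

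*Protocol article*

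**What the plan says.** For the primary outcome, under Statistical Analysis for the Primary Objective: "A subject-specific random intercept logistic model will be used to assess and test, using a 5% two-tailed threshold of significance". Under Statistical Analysis for the Secondary Objectives, the analysis of ASAS40 and partial remission "will be performed using similar random effect logistic models as for the primary objective", and the computing is to be done "using lme4 and lmerTest packages for the mixed effects models". The same section repeats the analyses in the radiographic and non-radiographic subgroups.

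Under Secondary Endpoints, each outcome is collected at the end of each period, so each patient contributes two binary observations. Partial remission needs a value below 2 on a 0–10 scale "in each of the 4 ASAS domains (patient’s global assessment, pain, BASFI, and inflammation". Inclusion Criteria ask for patients "having a total BASDAI score ≥4 (0–10) at baseline and a score of global pain ≥4 (0–10".

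The article gives no expected rate for either secondary outcome. It does not say how the mixed-model likelihood is approximated, and it gives no rule for sparse data.

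**The concern.** A random-intercept logistic model with two observations per patient learns its random-intercept SD mainly from how many patients respond in both periods and how many in only one. When responders are few, that information rests on a handful of patients. lme4's default is the Laplace approximation, which is weakest in this setting: the SD can run to a very large value, and the treatment log odds ratio and its standard error go with it.

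Partial remission is the likely case. A patient entering with pain of 4 or more must lose more than half of it to fall below 2, and must also be below 2 in the other three domains. An ASAS40 responder, as the article defines it, is also an ASAS20 responder, so its dummy-period rate cannot exceed the 30% assumed for ASAS20. That is a ceiling and does not show that the rate is low.

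At stake is a false-positive remission claim, or an odds ratio nobody can interpret, from running the named package at its default settings.

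**Working it through.** **Inputs from the article** (Calculation Hypotheses for the Number of Participants Required and the Result): a correlation of 0.1 between a patient's two responses; response rates given as "30% ASAS20 responders in the dummy stimulation period vs. 50% with active simulation"; and the result that "a sample size of 90 subjects will provide 80% power"; 25% missing; 120 enrolled. The scale of the 0.1 is not stated; I take it as the correlation between the two binary responses.

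**Assumptions, because the article gives no figure:** response rates of 3% to 20% in both periods for the secondary outcomes; correlation 0.1 or 0.3; a Wald test, since no test is named for the binary models.

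**1. The plan's own figure.**
- Both respond: 0.5 × 0.3 + 0.1 × √(0.25 × 0.21) = 0.173.
- Discordant: 0.327 + 0.127 = 0.454; difference 0.20.
- McNemar normal approximation at n = 90: (√90 × 0.20 − 1.96 × √0.454) / √(0.454 − 0.04) = 0.576 / 0.644 = 0.90, which is 81.5% power.
- Simulated glmer fits give 80% with Laplace and with quadrature, and no runaway SD appeared at these rates.
- 90 / 0.75 = 120.

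The primary calculation reproduces.

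**2. How little data informs the SD.** With rate p and correlation r in both periods, P(both respond) = p² + r·p(1 − p) and P(discordant) = 2[p − P(both)]. Expected counts among 90:

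| Rate | r | Both periods | One period only |
|---|---|---|---|
| 5% | 0.1 | 0.7 | 7.7 |
| 10% | 0.1 | 1.7 | 14.6 |
| 10% | 0.3 | 3.3 | 11.3 |

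**3. Default glmer (Laplace), no true effect, n = 90, two-sided 5%.** Three sets of simulations: (a) treatment only, 104–120 trials per case; (b) treatment and period, 500 trials; (c) treatment and period, 250 trials.

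| Rate | r | Type I error: a / b / c | SD above 4: a / b |
|---|---|---|---|
| 3% | 0.1 | 4.8% / – / – | 45% / – |
| 5% | 0.1 | 8.6% / 12.4% / 10% | 45% / 50% |
| 10% | 0.1 | 12.5% / 15.2% / 14% | 54% / 52% |
| 15% | 0.1 | 8.3% / 7.2% / – | 23% / 17% |
| 20% | 0.1 | 5.7% / – / – | 3% / – |
| 10% | 0.3 | – / 22.8% / 18% | – / 91% |
| 20% | 0.3 | – / 9.4% / – | – / 36% |

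At a true 5% the simulation standard error is √(0.05 × 0.95 / 120) = 2.0 points in (a), 1.0 in (b) and 1.4 in (c). In (a) alone only the 10% case is clearly above 5%; (b) and (c) confirm it and add the 5% case. Warnings appeared in about 1% of the null fits in (a) and 2–6% of fits in (b), so the failure is mostly silent.

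**4. Same model, 15-point adaptive quadrature.** Set (a): type I error 4.4%, 4.2% and 6.7% at rates of 5%, 10% and 15%, with SD above 4 in 3%, 0% and 0% of fits. Set (b): 1.2–4.8%. Set (c): 1–3%. The 6.7% lies within simulation error of 5%. At a 3% rate problems remain: SD above 4 in 14% of fits, outright errors in 3%, type I error 7.9%.

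**5. Empty periods, which quadrature cannot cure.** P(no responder among n) = (1 − p)ⁿ.
- n = 90: 0.97⁹⁰ = 6% and 0.98⁹⁰ = 16%. For either period, treating them as independent: 1 − (1 − 0.0645)² = 12% and 1 − (1 − 0.162)² = 30%.
- An assumed subgroup of 45 at 3%: 0.97⁴⁵ = 25%; either period, 1 − (1 − 0.254)² = 44%.

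In such a data set the odds ratio is infinite or zero and a Wald test cannot reject.

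**The case against.** The strongest objection is that the article names neither the Laplace fit nor the Wald test. A condensed article may leave the approximation and any sparse-data rule to the full protocol or the SAP, and an analyst who sets quadrature there has no problem at rates of 5% or more. This stands as a limit on the point: it shows what the named package does at its default, and it does not show that the trial will be analysed that way. The point survives because the article does fix the model and the package, and following it literally can mislead with little warning.

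Three stronger readings are tempting, and the documents support none of them.
- A reader might infer that a random-intercept logistic model is wrong for uncommon outcomes. The quadrature results contradict that at rates of 5% or more.
- A reader might infer that ASAS40 is affected as surely as partial remission. No ASAS40 rate is given. At 20% in both periods with correlation 0.1 the default fit behaves, and at 15% versus 30% Laplace and quadrature both give 73% power.
- A reader might take 0.1 as the plan's correlation for these outcomes. It was assumed for ASAS20 only, and the true value could be higher or lower.

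It can also be said that an exact paired test gains little when events are very rare. That is correct: five discordant patients all in one direction give a two-sided p of 2 × (1/2)⁵ = 0.0625.

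**Conclusion.** The concern holds for partial remission if its rate is about 10% or less and lme4 is run at its default. At n = 90 and correlation 0.1, about half of fits then have a random-intercept SD above 4. At rates of 5% to 10%, type I error is about 9–15% against a nominal 5%, and about 18–23% at a 10% rate with correlation 0.3. At 3% the SD still runs away, but the one simulated case showed no excess of rejections; the difficulty there is an uninterpretable estimate or an empty period.

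ASAS40 is exposed only if its rate is below about 15%, or near 20% with correlation about 0.3. The primary analysis is not affected at its own assumptions.

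The size rests on assumed rates, on the correlation being that of the binary responses, and on a Wald test. The fault is in the default approximation and not in the planned model. It concerns two of many secondary outcomes, but it is worth correcting because it is nearly silent and cheap to remove.

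**What to change.** In Statistical Analysis for the Secondary Objectives:

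1. State that the binary mixed models are fitted by adaptive Gauss–Hermite quadrature, for example with nAGQ of 15 or more in glmer.
2. For partial remission, and for ASAS40 if responders are few or a period has none, report an exact paired test by sequence (Mainland–Gart) with a paired risk difference and its confidence interval. Apply the same rule in the radiographic and non-radiographic subgroups.
3. Keep the quadrature model as the main analysis wherever it is estimable.

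The cost is two or three sentences and a little programming; the primary analysis and sample size do not change. The exact test has two drawbacks. It is conservative, with an actual size of about 1–2.5% at rates of 5% to 15%. It also uses only patients with both periods observed, which matters when 25% missing is expected. For these reasons it should be the fallback and not replace the model.

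### Separate 5% tests in radiographic and non-radiographic patients are subgroup analyses, not sensitivity analyses, and do not show whether the effect differs by form of disease

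*Protocol article*

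**What the plan says.** Two statements under *Statistical Analysis for the Secondary Objectives* in the protocol article matter here.

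- On the scope of the analyses: "The analyses for the primary and secondary outcomes will be also performed in subgroups of patients". The groups and the label follow: "patients with radiographic forms of the disease and patients with non-radiographic forms of the disease), as sensitivity analyses".
- On the significance level: "All statistical comparisons will be performed at the 5% level of significance". Nothing exempts the analyses by form.

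The sample size section plans for all patients together. It assumes "30% ASAS20 responders in the dummy stimulation period vs. 50% with active simulation" and states that "simulations have shown that a sample size of 90 subjects will provide 80% power". It gives no power for either form. The eligibility criteria admit both forms, and no expected proportion of each is given.

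**The concern.** A sensitivity analysis puts the same question to the data under different assumptions, to see whether the answer is robust. Restricting the data to one form of disease changes the population and therefore the question. The label has consequences: a reader who takes these runs as robustness checks will see a non-significant result in one form as a weakness of the overall finding, when it may reflect nothing but the smaller sample.

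The method has the matching fault. If one form gives p < 0.05 and the other does not, that is no evidence that the effects differ. The question is answered by comparing the two effects directly, through an interaction. Two verdicts at 5%, each from part of a sample sized for one overall test, will often disagree by chance. At stake is how a reader interprets the effect in radiographic and non-radiographic disease, for ASAS20 and for every secondary outcome.

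**Working it through.** **Inputs from the sample size section.** Response 30% under dummy and 50% under active stimulation; within-patient correlation 0.1; two-sided 5%; 90 evaluable patients; 80% power; 25% missing. **Assumed:** the split between the forms, taken from 45:45 to 72:18.

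**Method.** Normal approximation for paired proportions (McNemar), as a stand-in for the random intercept logistic model.

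- Response in both periods: 0.3 × 0.5 + 0.1 × √(0.3 × 0.7 × 0.5 × 0.5) = 0.173.
- Response under active only: 0.5 − 0.173 = 0.327. Under dummy only: 0.3 − 0.173 = 0.127.
- Total discordance D = 0.327 + 0.127 = 0.454; difference d = 0.327 − 0.127 = 0.20.
- Power(n) = Φ[(d√n − 1.96√D) / √(D − d²)].

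**The plan's own figure.** At n = 90: (0.2 × 9.487 − 1.96 × 0.674) / 0.644 = 0.90, so power is 81.5%, close to the stated 80%. Enrolment of 90 / 0.75 = 120 also agrees. The whole-sample calculation is sound.

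**Same true effect in both forms.** With power a in one form and b in the other, the two forms being independent, P(exactly one significant) = a(1 − b) + b(1 − a).

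| Assumed split | Power, larger / smaller form | Both significant | Exactly one | Neither |
|---|---|---|---|---|
| 45:45 | 0.513 / 0.513 | 0.263 | 0.500 | 0.237 |
| 54:36 | 0.591 / 0.426 | 0.252 | 0.514 | 0.235 |
| 63:27 | 0.661 / 0.331 | 0.219 | 0.554 | 0.227 |
| 72:18 | 0.721 / 0.231 | 0.167 | 0.618 | 0.215 |

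Simulating the paired test gives 50%, 51%, 57% and 63% for exactly one. Among simulated trials with a significant overall result, the figure runs from 56% at 45:45 to 73% at 72:18.

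A simulated likelihood-ratio test in a random intercept logistic model (1,500 runs) is somewhat more powerful: 84% at n = 90 and 57.5% at n = 45. At 45:45 that gives 2 × 0.575 × 0.425 = 49% for exactly one. The conclusion does not depend on the approximation.

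**No effect in either form.** P(at least one form significant on ASAS20) = 1 − 0.95² = 9.75%; the simulation gives 9.3% to 10.2%.

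**What an interaction test could detect.** Take the full effect (0.20) in one form and none in the other, with the same discordance of 0.454 in the form without an effect. On the risk-difference scale, SE = √[(D − d²)/n₁ + D/n₂], and power = Φ(0.20/SE − 1.96).

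- 45:45: SE = √(0.414/45 + 0.454/45) = 0.139; power 30%.
- 63:27, effect in the larger form: SE = √(0.414/63 + 0.454/27) = 0.153; power 26%.

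**The case against.** The strongest reply is that this is a condensed article whose analysis plan is not shown. That plan may add an interaction term and give the subgroup results exploratory status. The sentence does not exclude either, and calling the runs sensitivity analyses may be meant to mark them as merely supportive. This stands as far as it goes: the absence of an interaction test from an article is not in itself a fault. What the article does fix is separate analyses by form, a label that does not fit them, and a 5% level for all comparisons. An analysis plan that did better would have to depart from this text.

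Three stronger readings are tempting, and the document does not support them.

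- A reader might infer that the sponsor plans to claim efficacy in one form only. No passage says so. Neither the primary nor the secondary objectives mention form of disease, and the main analysis is in all randomized patients.
- A reader might infer that one particular false verdict is the expected result. At 45:45 the 50% is the sum of two opposite patterns of 25% each, against 26% for both forms being significant. One pattern dominates only at uneven splits: at 63:27 the larger form alone is significant in 0.661 × (1 − 0.331) = 44% of trials.
- A reader might extend the point to the number of unadjusted secondary endpoints in the full population. That is a separate matter. Unadjusted secondaries beside a single primary are common practice, and nothing in the article gives them confirmatory standing.

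**Conclusion.** The point holds as one about the analyses by form. The label is wrong, and separate 5% tests cannot show whether the effect differs between the forms. With an identical true effect in both, exactly one form would be significant in about half of trials at an even split and in 62% at 72:18. With no effect, the chance of at least one significant form on ASAS20 is 9.75%, not 5%. These figures rest on the plan's own response rates and correlation, on 90 patients with both periods evaluable, and on assumed splits.

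The primary intention-to-treat test, its significance level and the sample size are unaffected. The fault should be corrected, but it does not threaten the trial's main conclusion.

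**What to change.** In the analysis plan, before unblinding, replace the subgroup sentence and state that the replacement supersedes the article:

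- Call the analyses in radiographic and non-radiographic patients exploratory subgroup analyses.
- Assess difference by form with a treatment-by-form interaction, together with the main effect of form, in the mixed model fitted to the full population.
- Report the effect in each form with its 95% confidence interval and no separate significance verdict, and exempt these analyses from the general 5% rule.

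This needs only wording and one further model term: no patients, visits or data beyond the radiographic status already collected at inclusion. The cost is that no stand-alone claim of significance can be made in a subgroup. The interaction test is also weak here, with 26% to 30% power even when the whole effect lies in one form, so the plan should say that a non-significant interaction does not show equal effects.

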### Quality Control and Insurance

For this Minimal Risks and Burden research study, the appropriate quality control level has been determined based on the impact and the budget of the research. Assistance Publique-Hôpitaux de Paris (AP-HP) is the sponsor of this study and, by delegation, the DRCI (Clinical Research and Innovation Department) carries out the study’s missions in accordance with Article L.1121-1 of the French Public Health Code. Assistance Publique–Hôpitaux de Paris (AP-HP) has taken out insurance with HDI–GLOBAL SE through BIOMEDIC-INSURE for the full study period, which covers its own public liability and that of any collaborator (physician or research staff), in accordance with Article L.1121-10 of the Code de la Santé Publique (French Public Health Code). A Clinical Research Associate (CRA) appointed by the sponsor will be responsible for the good completion of the study, for collecting, documenting, recording and reporting all handwritten data, in accordance with the Standard Operating Procedures applied within the Clinical Research and Innovation Department. The investigator and the members of the investigator’s team agree to make themselves available during regular Quality Control visits carried out by the Clinical Research Associate.

## Conclusion

Current pharmacological management of inflammatory rheumatism and in particular axial SpA remains imperfect. Only 50% of patients respond to the most effective biotherapies, and many of them are only partially relieved (Braun and Sieper, 2002; Wendling and Prati, 2011). In addition, these are extremely expensive treatments that expose them to the risk of potentially serious side effects (de Koning et al., 2018; Lopez-Medina et al., 2018; Molto et al., 2018; Smolen et al., 2018; Wendling et al., 2018). The efficacy of non-invasive VNS therapy in patients with axial SpA has never been studied. This study will be the first to assess its benefit-risk balance through a rigorous randomized double-blind trial. This multi-center study includes 16 rheumatology centers in public hospitals in France, mostly university hospitals, all with good experience in conducting clinical trials. Our goal is to demonstrate the efficacy of non-invasive VNS as a treatment for axial SpA, especially in cases with resistance to biotherapies. We also expect improved quality of life and reduced short-term and long-term osteo-articular structural consequences in patients receiving VNS therapy. Proving efficacy of non-invasive VNS for reducing inflammation and its consequences in humans would open the way to clinical trials in other chronic inflammatory diseases.

